**Secondary outcome measures: clinical effectiveness of the intervention (observational comparison)**	
**Change in healthy lifestyles and cardiovascular risk factors** of high risk patients exposed to the intervention programme 12 months after exposure	
• Adherence to recommendations on physical activity and healthy diet:	
i) % who meet the recommended level of physical activity (150 min/week of moderate physical activity or 75 min/week of intense physical activity) , among those who did not meet it at recruitment;	Baseline and 12 months after programme exposure
ii) % who meet the recommended level of fruit and vegetable intake (5 portions/day), among those who did not meet it at recruitment. •Changes in physical activity (minutes of moderate to vigorous physical activity) or in fruit and vegetable intake	
• % whose BMI decreases by 5% by 12 months after the intervention • potential effects of the preventative intervention on other cardiovascular factors including cholesterol and triglyceride levels, as well as BMI and blood glucose (data derived from the annual clinical follow-up)	Electronical Health Record

Bolded text refers to the outcome dimensions composed of multiple indicators

Underlined text refers to possible T2D risk screening strategies to be adopted by centres

Patients exposed to the intensive intervention for the promotion of healthy lifestyles (i.e. the prescription of lifestyle change) in each centre/group will be followed-up every year in the centre with measurement of clinical parameters and the assessment of physical activity and diet with the *Prescribe Vida Saludable* (Prescribe Healthy Lifestyle) questionnaires [43], incorporated in the electronic health record (Table 2).3.Associated factors

In order to analyse the potential associated or modifying characteristics of the effect that the implementation strategy and, within it, the procedures for creating the community of practice could have on clinical practice in the primary prevention of T2D and on clinical outcomes, we studied various different factors at centre, health professional and patient levels:Health centre-based factors: Organisational willingness to change measured with the *Organizational Readiness for Knowledge Translation* (OR4KT) questionnaire [44], the Spanish version of the OR4KT instrument comprising 59 items assessing 6 dimensions and 23 sub-dimensions related to organisational predisposition to knowledge translation: organisational climate, organisational support, contextual factors, change content, leadership, and motivation; leadership assessed with the *Implementation Leadership Scale* (ILS) questionnaire [45]; and various characteristics of the primary care centres, namely, number of registered patients, number of healthcare professionals, mean number of registered patients per family doctor, and a socioeconomic deprivation index for the catchment area that combines variables related to employment (unemployment rate, manual and short-term employment) and education (educational attainment rate among young people and overall).Healthcare professional-related factors: sociodemographic variables (age, sex, professional group, etc.); and professionals’ healthy lifestyle behaviours; and Attitudes, knowledge and skills in the promotion of healthy habits in the clinical context, measured through the *Preventative Activity Questionnaire* [46].Patient-level factors: sociodemographic variables (age, sex, socioeconomic level- deprivation index, etc.); active health problems-morbidity (Adjusted Clinical Groups-ACG, etc.); and frequency of attendance.

Health professionals will be surveyed to obtain information related to the variables at health centre and professional level before the execution of the strategy, immediately after it and 12 months after the introduction of the programmes in the centres.4.Fidelity of the implementation strategy

In order, on the one hand, to facilitate the replication, dissemination and future scaling of both the implementation strategy and specifically, within it, the engagement procedure used (e.g. establishment of a community of practice, execution of collaborative dynamic sessions); and on the other, to assess the degree to which what has been carried out has adhered faithfully to the plan, the process of executing the implementation strategy will be exhaustively documented and subsequent described by health centre and professional group:Number of centres included out of all those approachedPercentage of health professionals who collaborate across all the centresNumber of actions carried out (training, work sessions, etc.), and final duration compared to that originally anticipated (exposition to the implementation strategy)Participation of collaborating health professionals in each actionAssessment of the content and usefulness of the actions by health professionalsResources allocated to the execution of the strategy in the health centres: actions and resources for the planning, organisation and execution of sessions; support materials, dedication of external facilitator, organisational support resources (freeing up of leader’s time, coverage of services, etc.)

The fidelity of the execution of the strategy and active ingredients will be assessed by triangulation of three sources of information: the protocol for the implementation strategy and the specific agendas of the working sessions; minutes, reports and other material produced in the sessions; and audio recordings of the sessions, which will be made for evaluation purposes with prior consent of the parties involved, and safeguarding the confidentiality of the information and data.5.Qualitative evaluation

Additionally, we will carry out a qualitative evaluation of the feasibility and impact of both the strategy and the clinical intervention on the optimisation of the care practice for the primary prevention of T2D. Specifically, we will conduct semi-structured interviews with key individuals to explore the following:The perceived feasibility (barriers and facilitators), results observed and satisfaction of healthcare professionals, concerning the implementation strategy and the community of practice developed and the integration of the intervention programme, carrying out at least 2 interviews per participating centre (total of 18 interviews). The scripts of key-informant interviews will be theoretically-grounded, based in both the TDF and CFIR frameworks [37, 38].The satisfaction of users exposed to the programme with the intervention received and the impact of thereof on changes in their lifestyle habits, again carrying out at least 2 interviews per participating centre (total of 18 interviews): 1 patient who has managed to change their lifestyle habits and another who has not.

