Specific objectives are the following:To estimate the effectiveness attributable to the strategy for engaging health professionals in the improvement of the clinical practice for preventing T2D in high risk individuals, comparing the following implementation indicators between the centres assigned to the sequentially facilitated collaborative model strategy and those assigned to the globally facilitated collaborative model strategy.To estimate the potential clinical effectiveness of the intervention programmes comparing the proportion of users who change their lifestyle habits (physical activity and diet) and lose 5% of their body weight (a) observed in the population exposed (pre-post comparison) in both groups and (b) comparing the figures obtained in the programmes following the sequential vs the global strategy.To analyse the factors associated with successful implementation results in the implementation strategy in general and in the engagement procedures assessed in particular, at the organisational collaborating health professional and exposed patients levels.To explore the perceived feasibility and satisfaction of health professionals and users exposed with the implementation processes and the intervention programmes.

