Regarding the secondary outcome variables, the percentages (e.g. % of patients who meet recommendations on physical activity) were compared using chi-square or non-parametric tests. Quantitative variables were compared using t-tests (comparison of the means). For these outcome measures, pre-post differences and differences between study groups will be estimated, and 95% confidence intervals (CIs) will be calculated on an intention-to-treat basis. Stratified analysis will be performed, mixed-effects generalised models will be built to estimate the differences between the groups adjusted for factors that confound or moderate the effect of the intervention (baseline demographic and clinical characteristics) and adjusted differences, adjusted odds ratios (ORs) and 95% CIs will be calculated at the patient level, taking into account the hierarchical and multicentre structure of data. To explore a potential modifying effect of the intervention on clinical outcomes obtained attributable to the procedure for creating the interprofessional community of practice, we will conduct comparisons by intervention protocol between groups using matching by propensity scores calculated on the basis of the characteristics of patients recorded in their health record. This will permit us to analyse the association between the actual intervention dose received (assessment of lifestyle habits, assessment of habits plus advice, and assessment of habits plus advice plus prescription) and the event of interest (change in lifestyle habits or weight loss) as a function of one or other engagement procedure, pairing patients participating in one or another comparison group in a 1:1 ratio on the basis of them having a similar probability of having received said treatment or intervention dose.

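### Two secondary adherence outcomes start at 0% by definition, so their planned pre-post difference can only show improvement

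*Protocol article*

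**What the plan says.** Table 2 of the protocol article lists the secondary outcomes as change "of high risk patients exposed to the intervention programme 12 months after exposure". Its two binary adherence items, one for physical activity and one for fruit and vegetables, are each percentages taken "among those who did not meet it at recruitment". The timing given is "Baseline and 12 months after programme exposure". The lines that follow (change in activity minutes or in intake, a 5% fall in BMI, other cardiovascular factors) carry no such restriction.

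Specific objective 2 (Background) estimates clinical effectiveness from the share of users who change their habits or lose weight. Part (a) is what is "observed in the population exposed (pre-post comparison) in both groups"; part (b) compares the sequential and global strategies.

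For secondary outcomes, the Analysis section says that "the percentages (e.g. % of patients who meet recommendations on physical activity) were compared using chi-square or non-parametric tests", and then: "For these outcome measures, pre-post differences and differences between study groups will be estimated", with 95% confidence intervals.

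Both groups receive the same implementation strategy and differ in the order in which professionals are engaged (Background; Random allocation; Implementation strategy). No unexposed group is described for part (a).

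**The concern.** A subset chosen for being below a threshold has 0% above it at the time of choice. A later reading can leave that figure at zero or raise it, but cannot lower it. Patients who met the level at recruitment and later fell below it are outside the denominator, so deterioration is invisible. Activity and diet come from questionnaires, and two readings a year apart will not agree perfectly, so some patients picked for a low reading will be above the threshold next time without any effect of the programme.

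With no unexposed group, nothing in the pre-post comparison separates this movement from a real effect. Both groups could report a gain on these two items, with a confidence interval clear of zero, under a programme that did nothing. Readers could take that as evidence for objective 2(a).

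**Working it through.** The article states no figure for this comparison, so there is none to reproduce. The check has three steps.

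**1. Do the restriction and the pre-post use meet on the same outcomes?** Table 2 fixes the denominator and gives baseline and 12 months as the timing. The Analysis section names the percentage meeting the activity recommendation as its example of a secondary percentage, then plans pre-post differences for these outcome measures. Objective 2(a) makes pre-post comparison an aim. As written, the restricted percentages fall within the pre-post analysis.

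**2. What does the restricted percentage show when the population does not change?**

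Assumptions, none of them in the article: the underlying measure is bivariate normal, with the same mean and SD at both times and correlation r; a share p meets the level at each time.

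- Threshold: c = Φ⁻¹(1 − p)
- Below at both times: B = Φ₂(c, c; r)
- Apparent conversion among those below at baseline: 1 − B/(1 − p)
- Lapse among those meeting at baseline: ((1 − p) − B)/p

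Example with p = 0.40 and r = 0.6: c = 0.253 and B = 0.4574.

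- Conversion = 1 − 0.4574/0.60 = 23.8%
- Lapse = (0.60 − 0.4574)/0.40 = 35.6%
- Net change in all patients = 0.60 × 23.8% − 0.40 × 35.6% = 14.3% − 14.3% = 0 (14.26% each way before rounding)

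Apparent conversion with no population change:

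| Share meeting level, p | r = 0.4 | r = 0.6 | r = 0.8 | r = 0.9 |
|---|---|---|---|---|
| 20% | 15.5% | 12.6% | 8.9% | 6.3% |
| 30% | 22.6% | 18.2% | 12.7% | 8.9% |
| 40% | 29.7% | 23.8% | 16.5% | 11.6% |
| 50% | 36.9% | 29.5% | 20.5% | 14.4% |

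The range is 6.3% to 36.9%. At r = 1, where every reading is perfectly stable, it is 0%.

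**3. Would it look like a finding?** Assume, for illustration, 100 patients in the subset and 15 crossing the threshold by chance. The 95% CI is 0.15 ± 1.96 × √(0.15 × 0.85/100) = 8.0% to 22.0%. All 15 discordant pairs go the same way, because the other direction is impossible, so exact McNemar p = 2 × 0.5¹⁵ = 0.00006.

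**The case against.** The strongest reply is that these items are conversion rates among patients with room to improve, a legitimate description that matches the objective's wording about users who change their habits. No sentence states a test of 0% against the 12-month figure. The Analysis section speaks of percentages and quantitative variables together, and its own example does not repeat the restriction. That leaves room for another reading. But Table 2 times the items at baseline and 12 months, and the analysis promises pre-post differences for these outcomes, so the article needs rewording on either reading.

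Several limits stand:

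- A reader might infer that all lifestyle outcomes, or objective 2(a) as a whole, are undermined. The article does not support that. Only the two binary items are restricted; the continuous activity and intake changes can fall as well as rise, and the weight and risk-factor outcomes carry no such selection.
- A reader might infer a bias between the strategies. The restriction applies equally to both groups, so neither gains a built-in advantage from it, although lapses are still ignored.
- A reader might infer that improvement appears even if no patient's reading moves. It does not: the artefact needs within-person variation.
- The cancelling of conversion and lapse in all exposed patients depends on those patients not having been selected on a low reading. Exposure means receiving a lifestyle prescription, and the recommended intervention includes assessing habits, so such selection is possible.
- The outcomes are secondary and labelled observational. The main implementation outcomes and the sample size are untouched.

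**Conclusion.** The point holds for the pre-post estimate of the two binary adherence outcomes, and only there. That the baseline is 0% and the difference cannot be negative follows from the definition and needs no assumption. That chance movement produces apparent improvement needs only imperfect agreement between readings, which is to be expected of questionnaires.

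The size cannot be fixed from the article. The 6-37% range rests wholly on the assumed shares, correlations and normal model; it shows that the artefact could be large enough to be taken for a benefit, not what it will be. These two items cannot support a pre-post conclusion about effectiveness. The remaining secondary outcomes do not share this defect as written. Secondary status limits the damage but does not make the estimate valid.

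**What to change.** Reword Table 2 and the secondary-outcome part of the Analysis section:

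- For the pre-post part, report the percentage meeting each level at baseline and at 12 months in all exposed patients with both readings, as a paired net change with a 95% CI.
- Beside it, show conversion among those below the level at baseline and relapse among those meeting it.
- Keep the restricted percentage for the between-group comparison or as description, and draw no pre-post conclusion about effectiveness from it.
- State that the net change remains uncontrolled for time trends, and may keep some regression to the mean if prescription depends on a low baseline reading.

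The same questionnaire data serve, so the cost is wording. The downside is that the reported change will look smaller.

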#### Users of primary care services

All the patients aged between 45 and 70 years old who seek medical attention in the participating centres at least once with a high risk of developing T2D and/or with moderate hyperglycaemia (high baseline glucose levels or glucose intolerance), but no diagnosis of T2D documented the medical record, will be candidates to participate in the T2D prevention programme.

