### Recommended clinical intervention based on evidence and clinical practice guidelines

Based on the available scientific evidence and clinical practice guidelines [2, 4, 13], three measures are recommended for the prevention of T2D in clinical settings:

(1) Screen for individuals with abnormal regulation of glucose or a high risk of developing T2D (fasting glucose ≥ 110–125 mg/dl, HbA1c ≥ 6%), with the following approaches being recommended: T2D screening as part of opportunistic screening for cardiovascular risk in individuals ≥ 45 years old or ≥ 30 years old with at least one known risk factor (e.g. hypertension); T2D screening based on a body mass index (BMI) ≥ 25 kg/m^2^ in individuals between 40 and 70 years old; or screening for T2D risk using the FINDRISC [13] scale in individuals between 45 and 70 years old. These last two procedures should be completed with a fasting glucose to discard T2D diagnosis.

(2) In patients identified as high risk, carry out a structured intensive programme focused on the prescription of personalised plans for lifestyle change (low-calorie and low-fat diets, and at least 150 min of exercise per week). This intensive intervention requires the assessment of lifestyle habits, personalised advice (tailored to the individual’s risk) and the setting of objectives and plans or prescription of a personalised intervention for lifestyle change. It should combine education with the use of theoretically-grounded evidence-based strategies for behavioural change and the introduction of changes in daily life.

(3) Ensure that the intervention is followed up to keep participants motivated, with frequent contact at the beginning and subsequently annual follow-up.

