**Effectiveness in the optimisation of clinical practice for the primary prevention of T2D (experimental comparison)**	
**Measures**	**Timing and Source**
**Coverage**: Screening indicators (depending on the screening strategy selected by the centre)	
*Case 1* *: T2D screening as part of opportunistic screening for cardiovascular risk in individuals aged ≥45 years or ≥30 years with at least one known risk factor:* • % of non-diabetic patients aged ≥30 years with a cardiovascular risk factor (e.g., hypertension or BMI ≥30 kg/m2 or hyperglycaemia) attending to family doctor office in whom clinical practice guidelines are followed in terms of T2D screening using fasting glucose levels in the previous year; • % of non-diabetic patients aged ≥45 years with no cardiovascular risk factor attending to family doctor office in whom clinical practice guidelines are followed in terms of T2D screening using fasting glucose levels in the previous 4 years.	
*Case 2* *: T2D screening based on a BMI≥25 kg/m2 in individuals aged 40 to 70 years:* • % of non-diabetic patients aged between 40 and 70 years attending to family doctor’s office whose BMI has been measured in the previous year, 12 months after the introduction of the T2D prevention programme in the centres;	Baseline and 12 months after the setting up of the programme
• % of non-diabetic patients aged between 40 and 70 years attending to family doctor’s office with a BMI≥25 kg/m2 who have been screened for T2D using fasting glucose in the previous year, 12 months after the introduction of the T2D prevention programme in the centres.	Electronical Health Record
**Implementation**: Execution of the elements of the intervention programme in high risk patients defined by the presence of prediabetes (fasting glucose 110-125 mg/dl)	
•% of patients whose physical activity levels and diet have been assessed, after the identification of T2D risk; •% of patients who have been given preventative advice concerning the need to increase physical activity and eat a healthy diet, after the identification of T2D risk;	
•% of patients who have been prescribed a plan for increasing physical activity and eating a healthy diet, after the identification of T2D risk;	Baseline and 12 months after the setting up of the programme
•% of high risk patients (fasting glucose 110-125 mg/dl) who have undergone annual testing of fasting glucose and HbA1c.	Electronical Health Record

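### The planned pre-post change in blood glucose is open to regression to the mean, because high risk is itself defined by a fasting glucose window

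*Protocol article*

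**What the plan says.** In Table 2 of the protocol article, the Implementation block concerns "high risk patients defined by the presence of prediabetes (fasting glucose 110-125 mg/dl"). The secondary block of the same table covers change in lifestyle and cardiovascular risk factors "of high risk patients exposed to the intervention programme 12 months after exposure". It includes "potential effects of the preventative intervention on other cardiovascular factors including cholesterol and triglyceride levels, as well as BMI and blood glucose", with data from the annual clinical follow-up in the electronic record. The timing given in that block is "Baseline and 12 months after programme exposure". Which reading counts as baseline is not stated.

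The Analysis section says of the secondary outcomes: "For these outcome measures, pre-post differences and differences between study groups will be estimated". It adds 95% confidence intervals and t-tests for quantitative variables. The second specific objective (Background) also plans an estimate "observed in the population exposed (pre-post comparison) in both groups", but the outcomes it names are lifestyle habits and 5% weight loss, not glucose.

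Two other sections describe entry more widely. Users of primary care services admits patients with "high risk of developing T2D and/or with moderate hyperglycaemia (high baseline glucose levels or glucose intolerance"). The section on the recommended intervention gives "fasting glucose ≥ 110–125 mg/dl, HbA1c ≥ 6" (per cent) as criteria and allows screening routes based on BMI or a risk score.

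Both arms apply the same implementation strategy and differ only in how professionals are engaged. Neither the Analysis section nor the limitations in the Discussion mention regression to the mean.

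**The concern.** Fasting glucose varies within a person from one test to the next. Patients picked because one reading fell between 110 and 125 mg/dl include many whose usual level is lower and whose reading happened to be high. Their next reading will on average be lower without any intervention. If the selecting reading is also the baseline, the pre-post interval addresses whether mean change is zero, which is not the same question as whether the programme lowers glucose.

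There is no unexposed arm from which the natural fall could be estimated and subtracted. Both arms could therefore show an apparent glucose benefit that comes from selection, and it could be read as clinical effectiveness of the programme.

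**Working it through.** **The plan's own figures.** The protocol gives no expected glucose change, SD or test-retest correlation, so there is nothing on glucose to reproduce. The only sample size for clinical outcomes is 308 per group with 10% loss (Sample size, for 5% weight loss). It is used here only to supply n: 308 × 0.9 = 277 per group, 554 pooled. Whether 308 follows from the stated 10% and 35% is a separate matter.

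**Inputs.**
- From the protocol: selection window 110-125 mg/dl; n = 277; ICC 0.03, applied here to the glucose change as an assumption; five and four centres per arm.
- Assumed: population mean μ 92-98 mg/dl, between-person SD 9-10, within-person SD 4-7, normal distributions, no programme effect, no drift, every patient selected on the window, qualifying reading used as baseline.

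**Formulas.** With total SD s = √(between² + within²) and test-retest correlation r = between²/s²:
- expected fall = (1 − r) × (E[X | 110 ≤ X ≤ 125] − μ)
- variance of change = (1 − r)² × Var(X | window) + s²(1 − r²)
- design effect = 1 + (m − 1) × 0.03, where m is patients per centre

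**Worked example: μ = 95, s = 10, r = 0.7.**
- The window is 1.5 to 3.0 SD above the mean. The mean inside it is 114.1 and the variance about 11.3.
- Fall = 0.3 × (114.1 − 95) = 5.7 mg/dl.
- Variance of change = 0.09 × 11.3 + 100 × 0.51 = 52.0, so SD = 7.2.
- Plain standard error = 7.2/√277 = 0.43. The fall is about 13 standard errors, so the probability of a significant fall is 1.00.
- With 4.5 centres per group, m = 277/4.5 = 61.6, the design effect is 1 + 60.6 × 0.03 = 2.82 and the standard error is 0.43 × √2.82 = 0.73. The fall is still about 8 standard errors.

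**Least favourable setting in the assumed range: μ = 98, between 10, within 4.**
- s = √116 = 10.77; r = 100/116 = 0.862.
- Mean in the window 114.8; fall = 0.138 × 16.8 = 2.3 mg/dl; SD of change 5.5; plain standard error 0.33; probability about 1.00.
- With four centres, m = 69.25, the design effect is 1 + 68.25 × 0.03 = 3.05 and the standard error 0.575. Probability 0.98.

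The largest fall in the range (μ = 92, between 10, within 7) is 7.5 mg/dl.

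**How far this depends on the assumptions.** A wider grid (mean 90-100, total SD 8-14, r 0.5-0.8) gives falls of 2.7 to 12.6 mg/dl. The lowest probability of a significant fall anywhere in the grid, with the design effect based on 4.5 centres per group, is:

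| Condition (n = 277 per group) | Plain t-test | With design effect |
|---|---|---|
| All selected on glucose, no drift | 0.999 | 0.96 |
| Untreated rise of 1 mg/dl | 0.99 | 0.73 |
| Untreated rise of 2 mg/dl | 0.65 | 0.29 |
| Half selected on glucose, no rise | 0.85 | 0.44 |
| No rise, grid widened to mean 105 and r 0.9 | 0.87 | 0.45 |

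Conditions can combine. With half selected on glucose and an untreated rise of 1 mg/dl, the pooled minimum (n = 554) is 0.36 by plain t-test and 0.16 with the design effect. With a rise of 2 mg/dl it is essentially zero.

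If a fresh reading taken after the qualifying one is the baseline, the rejection rate is about 0.05. The between-arm comparison of change, with equal selection and no clustering, rejects in about 0.06 of trials, so it carries no material bias.

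**The case against.** The 110-125 mg/dl definition heads the Implementation block of Table 2, while the secondary block speaks only of exposed high-risk patients, and two other sections admit patients by wider routes. The baseline reading is not specified, and a condensed article may leave that to the full protocol. The pre-post objective does not name glucose. The outcomes are labelled observational and their effects potential, no success criterion is tied to glucose, and between-group models adjusted for baseline characteristics are also planned.

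Most of this stands as a limit on size. A reader might infer that a false glucose benefit is nearly certain, or that the pre-post analysis cannot return a negative answer. The protocol does not support either: both need the qualifying value as baseline, practically all patients selected on the window, no upward drift, and variance figures that the protocol does not give.

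It does not remove the point. The general sentence on secondary outcomes in the Analysis section covers glucose. The Sample size section judges recruitment from attenders with prediabetes at 110 mg/dl or above, so much of the planned supply is selected on glucose. An observational label does not correct a bias whose direction is known. The adjusted models address differences between arms, not the pre-post change.

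**Conclusion.** The point holds in a limited form. Glucose both defines high risk and is a pre-post outcome, no unexposed arm exists, and nothing in the stated analysis removes regression to the mean from that estimate. The bias is towards a fall. Its size grows with the share of patients who entered through the window and depends on whether the qualifying reading is the baseline.

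Under the assumed inputs the fall is about 2.3 to 7.5 mg/dl, and a significant fall per group is very likely. Under the less favourable assumptions tabulated above it is much less so. All glucose means, SDs and correlations are assumptions.

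This concerns one secondary item. The main implementation outcomes are untouched. The between-arm contrast is largely unaffected if selection is similar in both arms; because centres choose their own screening route, that similarity should be checked rather than taken for granted.

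**What to change.** - State that the pre-post glucose change will not be interpreted as an effect of the intervention.
- Base any glucose claim on the between-arm difference adjusted for baseline glucose, with clustering by centre. The mixed models already planned can carry this.
- Define the baseline reading. Where the record holds a pre-exposure glucose that was not the qualifying test, use it.
- Report any pre-post glucose change as descriptive, with a sentence on regression to the mean.
- Optionally, as a sensitivity analysis, compare with the 12-month change in patients of the same centres who met the same criterion in a pre-programme year. State its limits: selection into prescription and into retesting, calendar change, and a comparator that is not untreated, since the Background reports that 30% of high-risk patients already receive some preventive advice.

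The cost is analysis wording and, for the optional part, one more extraction from records the research unit is already authorised to use. No new tests or patients are needed. The downside is a smaller, less favourable glucose result and, with a non-qualifying baseline, fewer patients.
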